| **4. Study protocol** |
| --- |
| 1. **Study population**   The study participants will be enrolled from the outpatient clinics of internal medicine department, family medicine department and Chinese medicine department of Linsen and Chinese medicine branch of Taipei City hospital.   1. **Study period**   2011/01/01 to 2012/12/31   1. **Study group**   2 groups   1. **Study duration**   16 weeks   1. **Study design**   Double blinded, randomized, and placebo-controlled trial   1. **Randomization**   The randomization sequence will be generated by a table of random numbers from the SPSS software. The allocator will have to call a central number to receive the next allocation sequence once a patient had been enrolled in the trial.   1. **Primary endpoint** 2. The percentage of change between baseline and 16 weeks in fasting triglyceride, total cholesterol, HDL, LDL. 3. Anthropometric measurements in terms of body weight, height, BMI, waist circumference, and hip circumference.   **8. Secondary endpoint**   1. The percentage of change between baseline and 16 weeks in fasting sugar, HbA1C, obesity related hormone peptides, such as leptin、adiponectin、ghrelin、fasting insulin resistance、APOB、APOA1, high sensitivity C-reactive protein (hsCRP) 2. HRQOL scores on the WHOQOL-BREF   Assessment method:  All measurements of biochemical characteristics and obesity-related hormone peptides of blood sample will be made at 0800-0900 after an overnight fasting using standardized methods. All measurements will do after an overnight fast using standardized method and will be performed in the beginning of the study and after 16 weeks of treatment. Height is measured with a wall-mounted stadiometer to the nearest 0.1 cm, weight is measured on a calibrated balance beam scale to the nearest 0.1 kg, and BMI is calculated according to the formula: BMI = body weight (BW) / height (kg/m^2^). We simultaneously collected the demographic data and fasting laboratory data such as blood sugar, creatinine, aminotransferases aspartate, aminotransferases alanine, uric acid, and plasma lipoproteins (triglyceride, cholesterol, HDL-cholesterol (HDL) and LDL-cholesterol (LDL)). Homeostasis model assessment for insulin resistance (HOMA-IR)【fasting glucose (mmol/l) × fasting insulin (UI/l)/22.5】 is used as insulin resistance measurement (25-26). All measurements will make at 0800-0900 after an overnight fast using standardized methods. A sample of whole blood was drawn and centrifuged at 4°C, and a 1-ml aliquot of serum was rapidly frozen (-80°C) for subsequent hormone analysis. The plasma adiponectin concentration will be measured by a radioimmunoassay kit (Linco Research, Inc., St. Charles, MO, USA). This kit employs the double-antibody/ polyethylene glycol technique using ^125^I-lableled adiponectin and a multispecies adiponectin rabbit antiserium. Plasma insulin levels will be measured using a commercially available radioimmunoassay (Linco Research, Inc., St. Charles, MO, USA). Plasma ghrelin levels will be measured with a commercially available radioimmunoassay (Linco Research, Inc., St. Charles, MO, USA), using ^125^I-lableled ghrelin as a tracer. The detection limitation for the assay will be 10 ng/ml.  **9. Safety evaluation**  （1）adverse event  （2）vital signs  （3）Physical examination  　 （4）laboratory evaluation including liver function and renal function  **10. Inclusion criteria**   1. Age between 20 and 65 years 2. Diagnosis of type 2 diabetes for more than one year 3. Body mass index (BMI) ≥ 18 kg/m2 and ≤ 30 kg/m2 4. Fasting triglyceride ≥ 150 mg/dl or fasting low-density-lipoprotein cholesterol (LDL) ≥ 100mg/dl 5. Willing to participate in and fill out questionnaires for this trial   **11. Exclusion criteria**   1. Serum alanine transaminase > 80 U/L 2. Serum creatinine > 1.8 mg/dl 3. Breast feeding or pregnancy 4. Heart failure, acute myocardial infarction, stroke, heavy injury 5. Any other conditions not suitable for trial as evaluated by the physician   **12. study protocol:**  All participants met the criteria will be asked to sign the informed consent form after letters explaining the purpose of the study sent to all the patients inviting their participation. Participants will be randomly allocated to receive a decaffeinated GTE EGCG (Group A) or a placebo (cellulose; Group B) for 16 weeks. Both experimental and placebo treatments were contained in the same opaque capsules, which will be administered by a blinded research assistant. Participants will be instructed to maintain an isocaloric diet and to continue their previous eating habits during the study period. Every four weeks, Participants will return to our clinics and report to the study center for adverse events and compliance assessment. Participants will be free to withdraw at any time. Throughout the study period, participants will be directed to continue taking the same dose of any prescribed hypoglycemic agents unless hypoglycemia or severe complications occurred, in which case they will be directed to reduce their dose immediately.  **13. Adverse event report**  We will assess any adverse event of the participants during the study and will discuss the necessary to drop out.  **14. Drop out/ withdraw criteria**   - 1. drug compliance < 60% or no willing to return during the study   2. pregnancy occurred during the study   3. major illness or hospitalization occurred during the study   4. the dose of antidiabetic or antihyperlipidemia medication changed during the study   5. not suitable to participant after doctor assessed during the study   6. lost of follow up or death   **15. Statistical analysis**   1. The data will be analyzed using SPSS software (version 17.0, Chicago, IL.) 2. Independent t-tests will be employed to examine the difference in anthropometrics, biochemical characteristics, obesity-related hormone peptides, and life-quality scores between EGCG group and placebo group. 3. Paired t-tests will be employed to examine the difference between before and after intervention for 16 weeks in both groups. 4. All p values will be two-tailed and α level of significance will be set at 0.05. 5. This study population will be “Intent to treat population” for analysis of therapeutic efficacy 6. The definition of ITT （Intent to treat population）is that participants take the study medication once.   **16. Preparation of samples and placebo**  Decaffeinated GTE was obtained by [name] from the Tea Research and Extension Station, Taoyuan County, Taiwan. It was extracted from dried leaves of green tea according to pre-set standard procedures. The decaffeinated GTE used in this study was standardized for several tea catechins in addition to EGCG. The placebo comprised pure microcrystalline cellulose. Capsules contained either 500 mg decaffeinated GTE extract or cellulose. This sample contains 57.12% EGCG (80.83% Total catechines.  [figure not shown]  （1）The machine was used to extract decaffeinated GTE.  [figure not shown]  （2）Placebo (B group) was made by cellulose. |

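### The between-group comparison is an unadjusted t-test with no stated outcome variable; adjusting for the baseline already collected would give more precision at almost no cost

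*Protocol*

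**What the plan says.** The between-group method is in Protocol item 15, point 2: "Independent t-tests will be employed to examine the difference in anthropometrics, biochemical characteristics, obesity-related hormone peptides". The same sentence also covers the quality-of-life scores and sets the EGCG arm against placebo. Point 3 adds a within-group test: "Paired t-tests will be employed to examine the difference between before and after intervention for 16 weeks in both groups". Neither point names a covariate, and baseline adjustment appears nowhere else in the Protocol.

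The endpoints are defined in items 7 and 8:

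- Lipids (primary): "The percentage of change between baseline and 16 weeks in fasting triglyceride, total cholesterol, HDL, LDL".
- Anthropometrics (primary): "Anthropometric measurements in terms of body weight, height, BMI, waist circumference, and hip circumference", with no change or time point stated.
- Biochemistry and hormones (secondary): "The percentage of change between baseline and 16 weeks in fasting sugar, HbA1C, obesity related hormone peptides", followed by further markers.
- Quality of life (secondary): "HRQOL scores on the WHOQOL-BREF", again with no change or time point.

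On timing, the assessment text under item 8 says that measurements "will be performed in the beginning of the study and after 16 weeks of treatment". Baseline values are therefore collected, and the paired tests in point 3 need them. For the WHOQOL-BREF a baseline is implied by these two statements and not stated separately.

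**The concern.** Point 2 leaves two things unsatisfactory.

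First, the test makes no use of the baseline as a covariate. A patient's lipid level at week 16 is predicted in part by the level at entry. A t-test on the week-16 value ignores that. A t-test on change subtracts the whole baseline, which over-corrects whenever the correlation is below 1. ANCOVA estimates the right amount of correction from the data and is the most precise of the three.

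Second, point 2 lists groups of variables and not endpoints. It can be read as a test on percentage change or as a test on week-16 values. The two do not have the same power, and which one is stronger depends on a correlation that the Protocol does not give. If nothing else settles the choice beforehand, it could be made after the data are seen. The paired tests do not help here, because they compare visits within an arm and not the arms with each other.

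**Working it through.** **Inputs.** The Protocol states no sample size, power, effect size, SD or baseline to week-16 correlation, so it has no figure to reproduce. The correlation r, the SDs, the effects, the numbers per arm and 1:1 allocation below are all assumptions. Two-sided alpha of 0.05 is from item 15, point 4.

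**Step 1: variance of the treatment effect**, with equal variance at both visits and the week-16 t-test set to 1:

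- t-test on week-16 value: 1
- t-test on change: 2(1 − r)
- ANCOVA: 1 − r²

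So ANCOVA relative to change is (1 − r²) / [2(1 − r)] = (1 + r)/2, and ANCOVA relative to the week-16 value is 1 − r².

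| r | ANCOVA / change | ANCOVA / week-16 value |
| --- | --- | --- |
| 0.3 | 0.65 | 0.91 |
| 0.5 | 0.75 | 0.75 |
| 0.7 | 0.85 | 0.51 |
| 0.8 | 0.90 | 0.36 |
| 0.9 | 0.95 | 0.19 |

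The two t-tests have equal variance where 2(1 − r) = 1, that is at r = 0.5. Below that the change score is the weaker choice, and above it the week-16 value is.

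**Step 2: the same in patients.** For an assumed effect of 0.5 SD of the week-16 value and 80% power, the number per arm is:

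| r | Week-16 t-test | Change t-test | ANCOVA |
| --- | --- | --- | --- |
| 0.3 | 63 | 88 | 58 |
| 0.5 | 63 | 63 | 48 |
| 0.7 | 63 | 38 | 33 |
| 0.8 | 63 | 26 | 23 |
| 0.9 | 63 | 13 | 12 |

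**Step 3: percentage change, by simulation.** Log-normal data, 50 per arm, 4,000 trials per scenario. The correlation follows from the between-patient and within-patient log-SDs.

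- Triglyceride: log-SDs 0.45 and 0.30, so r = 0.2025 / (0.2025 + 0.09) = 0.69; true effect −15%.
- LDL: log-SDs 0.24 and 0.20, so r = 0.0576 / (0.0576 + 0.04) = 0.59; true effect −10%.

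| Analysis | Power, triglyceride | Power, LDL |
| --- | --- | --- |
| t-test on % change | 45% | 44% |
| % change, adjusted for baseline | 49% | 50% |
| t-test on log change | 49% | 45% |
| log week-16 value on log baseline (ANCOVA) | 55% | 52% |

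The gain from adjustment must be read within one scale. For triglyceride it is 49 − 45 = 4 points on percentage change and 55 − 49 = 6 points on the log scale. For LDL it is 50 − 44 = 6 and 52 − 45 = 7. The Monte Carlo standard error of a single entry is about √(0.5 × 0.5 / 4,000) = 0.8 point. A repeat with 20,000 trials gave gains of 4.4 and 6.3 points (triglyceride) and 7.0 and 8.1 points (LDL). A t-test on week-16 values had about 28% power for triglyceride and 37% for LDL.

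**Step 4: a second set of assumptions.** With 40 per arm and a 12% reduction, adjusting percentage change for log baseline raised power as follows:

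- log-SD 0.25: from 59.4% to 71.0% at r = 0.5, and from 82.6% to 88.0% at r = 0.7
- log-SD 0.45: from 22.2% to 27.3% at r = 0.5, and from 35.4% to 39.2% at r = 0.7

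The gains are 11.6, 5.4, 5.1 and 3.8 points.

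**Step 5: validity.** With no true effect, the Step 3 scenarios gave type I error of 4.7% and 5.5% for the t-test on percentage change, and 5.1% and 4.9% for the t-test on week-16 values. These agree with the nominal 5%.

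**The case against.** The strongest reply is that nothing here is wrong. An unadjusted t-test in a randomised, placebo-controlled trial keeps its error rate, as Step 5 shows. That stands, and it limits the point to efficiency and specification.

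A second reply is that the natural reading of point 2 is a t-test on each endpoint as items 7 and 8 define it, and that the exact analysis variable may be set in a statistical analysis plan that is not shown. This stands in part. A reader might infer from the wording that raw levels are compared, but the text does not establish that. It is one of two readings, and the larger losses against week-16 values apply only on that reading. The choice of test is a different matter, because the Protocol itself fixes it.

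A reader might also infer that randomisation from a plain random-number list makes a baseline imbalance in lipids likely. The Protocol does not support this. Item 6 mentions random numbers and central allocation and is silent on blocks and strata. Blocking mainly controls group sizes and does little for lipid balance. Chance imbalance is in any case already allowed for in the t-test's error rate.

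Finally, the full gap between the t-test on percentage change and log-scale ANCOVA (55 − 45 = 10 points for triglyceride) should not be credited to baseline adjustment, since 49 − 45 = 4 of those points come from taking logs. The simulations also ignore the entry thresholds for triglyceride or LDL in item 10, which restrict the baseline range and can change r.

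**Conclusion.** The point holds as an improvement worth making. Point 2 of item 15 fixes a valid but less precise test and leaves the analysed quantity open, although the data for a better analysis are already collected. It does not show bias or an inflated error rate.

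Against a t-test on change, ANCOVA variance is 75% to 90% for r from 0.5 to 0.8. In power, adjustment adds about 4 to 8 points with 50 per arm. Over both sets of assumptions with r between about 0.5 and 0.7 it adds 4 to 12 points, so roughly 5 to 10 is a fair working figure. The gain is small against a change score when r is near 1, and small against the week-16 value when r is low. The direction does not depend on the assumptions, apart from ties at the extremes. The size does, and the Protocol offers nothing to narrow it.

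**What to change.** In item 15, point 2, name the analysed quantity for each endpoint and replace the independent t-test by ANCOVA with treatment as factor and the baseline value of the same variable as covariate. Report the adjusted difference with a 95% CI. For the lipids, choose one of two forms before unblinding:

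- **Percentage change adjusted for baseline.** Item 7 stays as written.
- **Log week-16 value on log baseline.** Here exp(coefficient) − 1 is the percentage difference between arms. The estimand becomes a ratio of geometric means, so item 7 must be reworded to match.

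For anthropometrics and the WHOQOL-BREF, state whether the outcome is the week-16 value or the change, and confirm that the WHOQOL-BREF is completed at baseline. Height is not a treatment outcome and needs no test. Keep the unadjusted t-test on percentage change as a supportive analysis.

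The cost is a change of wording in item 15, and in item 7 if the log form is chosen. No extra visit, measurement or patient is needed, and ANCOVA is a standard linear model that runs in the SPSS version named in item 15.

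### Within-arm paired t-tests stand at the same 0.05 level as the between-arm tests, with no statement of which carries the efficacy conclusion, in patients selected on two of the primary lipids

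*Protocol*

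**What the plan says.** The design is a "Double blinded, randomized, and placebo-controlled trial" with two groups. The lipid part of the primary endpoint is "The percentage of change between baseline and 16 weeks in fasting triglyceride, total cholesterol, HDL, LDL". One of the entry criteria (section 10, item 4) is "Fasting triglyceride ≥ 150 mg/dl or fasting low-density-lipoprotein cholesterol (LDL) ≥ 100mg/dl", so two of the four primary lipids also decide who enters. Under the assessment method, measurements "will be performed in the beginning of the study and after 16 weeks of treatment". No screening lipid measurement separate from baseline is described, and the protocol does not say whether the qualifying value serves as baseline.

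Section 15 then lists two families of tests side by side. Item 2 reads: "Independent t-tests will be employed to examine the difference in anthropometrics, biochemical characteristics, obesity-related hormone peptides, and life-quality scores between EGCG group and placebo group". Item 3 reads: "Paired t-tests will be employed to examine the difference between before and after intervention for 16 weeks in both groups". Item 4 covers both: "All p values will be two-tailed and α level of significance will be set at 0.05". Item 5 adds "This study population will be “Intent to treat population” for analysis of therapeutic efficacy", which names the population but not the test that decides efficacy. Neither family is called primary, and the paired tests are not called descriptive.

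**The concern.** A before-after test in one arm asks whether that arm changed. It does not ask whether EGCG changed lipids more than placebo did. Anything that moves both arms enters the paired test in full: regression to the mean, the effect of being in a trial, season. In the between-arm comparison it cancels on average.

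This trial is exposed because it selects on high values of its own endpoints. If the value that qualified a patient is also the baseline, triglyceride and LDL are expected to fall on re-measurement in both arms without any drug effect. The expected fall is the same in each arm; only the significance verdicts can differ, by chance. A significant result with EGCG and a non-significant one with placebo may then be read as efficacy although no difference between arms has been shown. As section 15 stands, nothing rules that reading out, and the endpoints most affected are primary.

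**Working it through.** **Reference figure.** The protocol gives no sample size, power, SD or effect size, so there is no figure to reproduce. From the document come the 0.05 two-sided level, the two entry cut-offs and the two measurement times. Everything marked as assumed below is not in the document.

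**Step 1: no drift at all.** With independent arms, the chance that exactly one paired test is significant in either direction is 2 × 0.05 × 0.95 = 0.095. For a significant *fall* with EGCG and none with placebo it is 0.025 × 0.975 = 0.024.

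**Step 2: a drift shared by both arms.** If each arm shows a significant fall with probability p, then P(EGCG only) = p(1 − p). At p = 0.1 this is 0.09, at p = 0.3 it is 0.21, and it peaks at 0.25 when p = 0.5. The cause of the drift does not matter.

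**Step 3: how large p is from selection on lipids.** Assumed:
- clinic LDL mean 90 to 105 mg/dl, SD 30
- triglyceride median 110 to 130 mg/dl, log SD 0.5
- LDL and triglyceride independent
- test-retest correlation r of 0.7 to 0.8
- 50 per arm, no drug effect, qualifying value used as baseline

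The expected fall is (1 − r) × (mean of entrants − clinic mean). Because a patient may qualify on either lipid, the mean LDL excess among entrants is SD × φ(c) × P(TG < 150) / P(entry), where c = (100 − mean)/SD and φ is the standard normal density. The term P(TG < 150) is the dilution caused by the either-or criterion.

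*High corner* (LDL mean 90, TG median 110, r = 0.7):
- c = 0.333 and φ(c) = 0.377
- P(LDL < 100) = 0.631; P(TG < 150) = 0.732; P(entry) = 1 − 0.631 × 0.732 = 0.538
- excess = 30 × 0.377 × 0.732 / 0.538 = 15.4 mg/dl
- fall = 0.3 × 15.4 = 4.6 mg/dl
- the SD of change among entrants is about 23.1, so the noncentrality is 4.6 × √50 / 23.1 = 1.41; noncentral t with 49 df gives p = 0.28
- EGCG only = 0.28 × 0.72 = 0.20

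*Low corner* (LDL mean 105, TG median 130, r = 0.8):
- c = −0.167 and φ(c) = 0.393
- P(LDL < 100) = 0.434; P(TG < 150) = 0.613; P(entry) = 1 − 0.434 × 0.613 = 0.734
- excess = 30 × 0.393 × 0.613 / 0.734 = 9.8 mg/dl
- fall = 0.2 × 9.8 = 2.0 mg/dl; noncentral t gives p = 0.11
- EGCG only = 0.11 × 0.89 = 0.10

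A simulation of two million people at each corner of the grid agrees with these LDL values. For triglyceride on the log scale it gives falls of 2% to 6% and p from 0.07 to 0.18, so EGCG only runs from 0.07 × 0.93 = 0.065 to 0.18 × 0.82 = 0.148.

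| Lipid | Fall by selection alone | Significant fall, per arm | Significant fall, EGCG only |
|---|---|---|---|
| LDL | 2.0 to 4.6 mg/dl | 11% to 28% | about 10% to 20% |
| Triglyceride | 2% to 6% | 7% to 18% | about 6% to 15% |

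**Step 4: other inputs.** A second simulation assumed LDL mean 110, SD 32; TG median 140, log SD 0.5; correlation 0.6 to 0.8 for LDL and 0.5 to 0.7 for log TG; and 30, 50 or 100 per arm. EGCG only was 5% to 18% across the two lipids.

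**Step 5: baseline measured separately from screening.** In the second simulation the mean fall is about 0 and EGCG only is about 2% to 3%, as in step 1.

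**Step 6: the between-arm test.** In every scenario of the second simulation, the independent t-test on change rejected in about 4% to 6% of trials, in line with its nominal level.

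**The case against.** The strongest reply is that the valid comparison is already planned. Item 2 comes first, covers the same classes of variable, and is not biased by regression to the mean. To claim efficacy from item 3, the authors would have to set item 2 aside. This stands, and it limits the point: the fault is an undefined role for item 3, not a missing comparison. The role of a secondary test is also often settled in a statistical analysis plan, which may exist but is not at hand. Even so, section 15 does fix one thing itself: the same level for all p values, with no ranking of the tests.

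Three stronger readings are tempting, and the protocol does not support them.

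- *A reader might infer that the paired tests are planned as efficacy tests.* Item 3 does not say so. It only fails to separate them from efficacy tests.
- *A reader might infer that regression to the mean acts in one arm only, or on every variable.* It acts on both arms alike, and mainly on triglyceride, LDL and what correlates with them. Selection on lipids says little about waist circumference, ghrelin or quality of life.
- *A reader might take the chance of significance in exactly one arm as the risk.* That is 2p(1 − p), and half of it is placebo-only trials, which would support no claim for EGCG.

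It is also fair to say that the size rests on the qualifying value being the baseline. With a separate baseline the selection effect disappears, although any other shared drift would still act as in step 2.

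**Conclusion.** The point holds in a limited form. Section 15 places an uncontrolled within-arm test beside the controlled one at the same level and does not say which decides efficacy. If the qualifying lipid value is the baseline, a significant fall with EGCG alone occurs without a drug effect in about 10% to 20% of trials for LDL and 6% to 15% for triglyceride, against 2.4% when there is no drift. These figures rest on the assumed clinic distributions, correlations and 50 per arm; the second set of inputs gives 5% to 18%. If baseline is measured separately, the figure is about 2% to 3%, and what remains is the general fault that a within-arm test does not answer the trial's question. The between-arm conclusion is sound in either case. The change is worth making because the two lipids are primary endpoints and the correction is nearly free.

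**What to change.** - In section 15 item 3, replace the paired t-tests by within-arm mean changes with confidence intervals, labelled descriptive, with no p values used for efficacy.
- State that every efficacy conclusion rests on the between-arm comparison.
- In item 2, replace the unadjusted t-test by an analysis of covariance on the baseline value already collected. The unadjusted test is unbiased over randomization, but if one arm happens to start higher on a lipid, that arm is expected to fall more; the adjustment deals with this.
- State whether the qualifying lipid value is the baseline value, so that readers can interpret the within-arm changes.

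The cost is a minor revision of the analysis text and a slightly different model. No extra patients, visits or measurements are needed.
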